### Study procedure

On the day of admission eligible patients will be informed about the study protocol. If they agree to participate in the study and sign and date the informed consent form, the following procedure will apply (Table 1):

**Table 1 Tab1:** Schedule of events

Procedures	Baseline (within 72 h prior to procedure)	Day of surgery	Postoperative stay in hospital	3 Months after surgery ± 2 weeks	6 Months after surgery ± 2 weeks	12 Months after surgery ± 2 weeks
Inclusion/exclusion	X	X				
Randomisation		X				
Informed consent	X					
Demographics	X					
Medical history	X					
Concomitant medications including use of analgesics or peripheral nerve block	X	X	X^d^	X	X	X
Physical examination (ROM)	X		X^d^	X	X	X
Laboratory tests (virology^a^, CBC^b^, clinical chemistry^c^)	X^a–c^		X^e,b,c^			
Coagulation parameters (INR, PTT)	X					
Treatment application		X				
Intraoperative data assessment		X				
Clinical outcome score assessment (KSS/KOOS)	X		X^f^	X	X	X
Surgical site assessment			X^d^	X	X	X
Wound healing assessment			X^d^			
Assessment of patient’s mobility on crutches (stairs)			X^d^			
Adverse events		X	X^d^	X	X	X
Assessment of physiotherapy treatments after rehabilitation				X	X	X
Calculation of overall costs of TKR						X

^a^Virology: Hep B/C and HIV screening

^b^CBC: Hb, leucocytes

^c^Clinical chemistry: CRP

^d^Assessment daily during the visits (except for Sundays as for the physical examination)

^e^Assessment on days 2, 4 and 6 (+/− 1 day) and on day 7

^f^Assessment on day 7

#### Preoperative examinations (baseline)

The preoperative examinations to establish baseline measures will include the following:Orthopaedic examination of the lower extremity, including measurement of ROM, and confirmation of the medical indication.Blood samples taken and tested according to in-house protocol. Relevant parameters for the study are: INR, PTT and complete blood count (CBC) without differential, including Hb and leucocytes. The amount of blood needed for this routine procedure is about 26.5 ml.Subcutaneous injection of certoparin-sodium (for example, Mono Embolex™) at a dose of 3,000 IU/day performed from the preoperative evening onwards. An equivalent drug might be used as an alternative, depending on the guidelines (for example, no preoperative administration in the case of some oral products).

The following general data will be collected on the corresponding case report form (CRF): patient ID; gender and date of birth; height and weight; BMI; medical history, especially regarding thromboembolic events; smoking status; comorbidities and concomitant medications. In addition, the following specific data will be assessed: indication(s) for TKR, Hb level (g/dl), C-reactive protein (CRP) (mg/dl), leucocytes (1/μl), virology (hepatitis B/C and HIV screening), haemostatic parameters (INR and PTT), ROM (angle of maximum flexion), details of medications used as prophylaxis against thrombosis, and assessment of KSS and KOOS.

#### Details of the operation and of EVICEL™ administration

Investigators will perform the operation according to the established in-house standard and the guidelines of the prosthesis manufacturer. The operation will follow a very strict protocol in order to minimise adverse factors. The prosthesis implanted will be the Stryker Triathlon™ system. All components are always cemented with antibiotic-containing cement (Refobacine Palacos). The operation will be performed in a bloodless field: prior to the skin incision, the tourniquet is set to 250 mmHg. During the operation haemostasis will be performed conventionally by electrocoagulation.

For the study group, haemostasis is extended by the use of EVICEL™ according to the manufacturer’s guidelines and recommendations. The application will be performed by the surgeons themselves. The first application takes place immediately after lavage, before implanting the prosthesis: 2 ml of EVICEL™ are sprayed into the popliteal fossa, which cannot be approached subsequently. Where cancellous bone surfaces are bleeding after cementation of the prosthesis, EVICEL™ is sprayed on those areas. After hardening of the bone cement, functional tests and conventional haemostasis are performed as usual. The second administration of EVICEL™ is carried out on the meniscal and capsular blood vessels as well as in the superior recess (a total of 2 ml). A wait of 2 min without any action is necessary before starting the suture. After suturing the joint capsule, 1 ml of EVICEL™ is sprayed into the subcutaneous tissue. Suction or swabbing must be strictly avoided in the areas where EVICEL™ has been administered.

In case of complications occurring during the administration of EVICEL™ (for example, intraoperative thromboembolic events or allergic reactions), the application will be stopped immediately in the subject concerned.

For both groups, a sterile compression bandage is placed after skin suturing. The tourniquet is then removed.

In order to ensure better comparability of the results, no wound drainage system will be used in this study as the drained volume depends on the hardly reproducible position of the drainage *in situ*.

The tourniquet must be removed after 2 h at the latest. If the operating time from incision to suturing exceeds 2 h, the tourniquet is removed earlier in the procedure. In this situation, the patient will be withdrawn from the study.

The following specific data concerning the operation are collected: duration of surgery; type of anaesthesia (spinal or general); management of fluid balance; use of tourniquet (pressure in mmHg and time in minutes); amount of EVICEL™ used (ml); intraoperative complications; use of peripheral/nerve blocks; number of allogeneic and autologous blood units transfused; and documentation of autologous retransfusion of blood collected during surgery.

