## Methods/Design

### Study design

This study will be a single-centre, parallel-design, randomised controlled trial (RCT) in which 68 patients undergoing TKR will be recruited according to the inclusion/exclusion criteria for RCTs, and treated within a 12-month period at the Department of Orthopaedic Surgery. It is registered in the German registry under number DRKS00007564. Ethical approval has been obtained from the Institutional Review Board of the Hannover Medical School under process number ‘6170 M mono’. The study will be conducted in accordance with the Helsinki Declaration.

Thirty-four (34) control patients will receive the standard orthopaedic surgery treatment (electrocoagulation). Another 34 will receive the same treatment as control patients plus 5 ml EVICEL™ applied during surgery and used according to the manufacturer’s instructions.

The main trial period is the stay in hospital for the surgery and postoperative surveillance. Follow-up examinations of all patients will be conducted 3, 6 and 12 months after surgery. With a recruitment period of 12 months and a follow-up period of 12 months, the total length of the study period is calculated to be approximately 24 months.

The study will be terminated when the necessary 34 patients per group have completed the study. Additionally, the sponsor has the right to terminate the study at any time for reasonable medical or administrative reasons. Also, the principal investigator can decide to terminate the study at any time for reasonable medical or administrative reasons.

The results manuscript will follow the advice from the CONSORT guide and its extension to cluster trials.

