### Study population

A total of 68 men or nonpregnant women scheduled for primary unilateral TKR will be recruited and treated in the context of this RCT.

The inclusion criteria are as follows:Men or women aged from 55 to 70 years on the day of the operation.Patients with an indication for primary TKR on the basis of diagnosed osteoarthritis, arthritis or avascular necrosis.Patients with intact medial and lateral collateral ligaments (to be diagnosed in the preoperative examination) who are planned preoperatively to receive a Stryker Triathlon CR or Triathlon PS system prosthesis.Patients willing to participate in this RCT and who have signed the informed consent form approved by the ethics committee.

The exclusion criteria are as follows:Patients participating in any other clinical trial within 30 days before inclusion or concurrent with this study.Pregnant or nursing women.Patients tested positive for HIV, hepatitis B and C.Patients with documented or suspected hypersensitivity to any of the active substances or excipients of EVICEL™, or to bone cement or its components.Patients with acute or suspected coagulation disorders and patients with preoperative blood parameters INR >1.4 or PTT >40 s.Concomitant medication within 7 days before surgery with substances that affect haemostasis, except for low molecular weight heparins or alternatives in prophylactic dosage indicated for standard thrombosis prophylaxis.Anaemic patients showing preoperative Hb levels <11 g/dl.Patients with a deficit in extension >15° or with a maximal flexion <90°.Highly obese people (BMI >35). Patients suffering from neuromuscular or neurosensory diseases. Patients with known active tumour disease or tumour-related diseases. Patients suffering from any significant concurrent disease, illness or psychiatric disorder that would compromise their safety or compliance, or interfere with consent, study participation, follow-up or interpretation of the results. Patients receiving a prosthesis different from the Stryker Triathlon CR or Triathlon PS system owing to intraoperative circumstances (for example, bone fractures or ligament insufficiencies). Intraoperative deviation from the agreed haemostatic procedure (for example, use of the tourniquet deviating from the agreement, for example in case of surgery lasting >2 h). Patients with surgery lasting >2 h will not be randomised.

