#### Statistical methods

The statistical analysis will be carried out at the end of the study; interim analyses are not intended. However, the analysis of the primary endpoint may be carried out earlier, as soon as the data from the last patient have been assessed. For this analysis, ANCOVA for Hb level differences baseline with respect to the detected minimum in the first 7 postoperative days for both treatment groups with adjustment for baseline Hb levels will be used. If the upper limit of the two-sided 95 % confidence interval (CI) of the difference in means between EVICEL™ and standard orthopaedic surgery as estimated from the ANCOVA model is <0, the superiority of EVICEL™ will be concluded. Missing values for Hb observations will be replaced by the last observation carried forward method (LOCF). If there are no postoperative Hb values available for a particular patient, that patient will be recorded as having the largest decrease in Hb of the control group.

AEs and SAEs will be evaluated descriptively by chi-squared tests.

For the secondary endpoints, the need for at least one transfusion will be analysed by odds ratios (OR) together with 95 % CIs. The ROM and the length of hospital stay will be analysed by *t*-tests. The total cost per patient will be analysed using Wilcoxon’s signed ranks test. Time until wound healing will be tested by log rank tests.

Secondary and tertiary analyses are exploratory and will be performed descriptively.

The *P* values will be assessed descriptively and will be deemed significant when *P* <0.05.

The primary analysis will be conducted on the intention to treat (ITT) population, that is, for all randomised patients. Sensitivity analyses will be performed in the per-protocol (PP) population, including all patients who completed the study according to the protocol.

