### Subject withdrawal

As the application of EVICEL™ is conducted only at a single time point in a three-step procedure, subjects cannot be withdrawn from the IMP treatment. The only exceptions are complications occurring during the operation, leading to an immediate cessation of EVICEL™ use.

Patients undergoing a thromboembolic or any other event demanding anticoagulation that exceeds the standard prophylaxis measures during the first 7 days after surgery will be recorded as having the smallest Hb value before anticoagulation. Patients receiving anticoagulation during the operation will be recorded as having the largest Hb difference of the control group. The same procedure applies to patients receiving any kind of blood product during or after the operation. Because in nearly all cases there will be a blood sample collection prior to a transfusion or to a change in anticoagulation medication, these patients are expected to account for <1 % of all patients and will be recorded separately.

The following procedure applies to patients receiving any kind of blood product or an extended anticoagulation medication during or after the operation. Patients receiving blood transfusions during the operation but before randomisation will not be randomised. Patients receiving blood transfusions during the operation and after randomisation will be recorded as having the largest Hb difference of the control group. Patients receiving a blood transfusion after the operation would require measurement of Hb level before transfusion. Patients deteriorating despite transfusion will be recorded as having the smallest observed Hb level. For each transfusion, the Hb value at the time of transfusion, the reason for the transfusion (with specification of the symptoms) and the time of transfusion will be documented precisely.

Patients with an intraoperative deviation from the agreed haemostatic procedure (use of EVICEL™, electrocoagulation, or of the tourniquet deviating from the agreement, e.g. in the case of surgery lasting >2 h) will not be enrolled. In most cases, it is foreseeable before randomisation that the operation will probably take longer than 2 h; therefore, those patients will not be randomised, and the percentage of subjects not included because of the duration of surgery is expected to be <1 %.

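### An operation over 2 h is given three incompatible dispositions, and removing a patient found to qualify only after the intraoperative randomisation conflicts with the all-randomised ITT analysis

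*Protocol article*

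**What the plan says.** The protocol article deals with long operations in three places.

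- Details of the operation and of EVICEL administration: "If the operating time from incision to suturing exceeds 2 h, the tourniquet is removed earlier in the procedure". The next sentence reads "In this situation, the patient will be withdrawn from the study".
- Study population, last exclusion criterion: "Patients with surgery lasting >2 h will not be randomised".
- Subject withdrawal: "Patients with an intraoperative deviation from the agreed haemostatic procedure (use of EVICEL™, electrocoagulation, or of the tourniquet deviating from the agreement", with an operation over 2 h as the example) are treated as not enrolled. The section adds that an overrun can usually be foreseen before randomisation, and it expects fewer than 1 % of subjects not to be included because of operating time.

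Under Randomisation/blinding, the surgeon obtains the allocation by phone during the operation, when EVICEL would be due, and is not blinded. The operative description puts the first spray before the prosthesis is implanted. It also says, for the study group, "A wait of 2 min without any action is necessary before starting the suture".

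Statistical methods then states: "The primary analysis will be conducted on the intention to treat (ITT) population, that is, for all randomised patients". The per-protocol set is used for sensitivity analyses.

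**The concern.** A patient can be in only one of three states: never randomised, randomised and analysed, or randomised and removed. The text assigns the same event to the first and, through the word withdrawn, possibly to the third, while the analysis section promises the second. The conflict has practical effect only if the event can come to light after allocation. Because randomisation is intraoperative, it can.

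What is at stake is who enters the primary comparison. A removal decided after allocation, in a theatre where the surgeon knows the arm, is the kind of selection that an all-randomised analysis is meant to prevent. With 34 patients per group, single patients carry visible weight.

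**Working it through.** **1. The plan's own figure.** Inputs from Sample size calculation: difference 37 − 25 = 12 g/l, SD 15 g/l, two-sided alpha 0.05, power 90 %, equal groups.

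- Normal approximation: n = 2 × (1.960 + 1.282)² × 15² / 12² = 2 × 10.51 × 225 / 144 = 32.8, so 33 per group.
- Exact noncentral t: 34 per group gives power 0.9015; 33 gives 0.893.

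The stated 34 per group is reproduced. No figure in the article is wrong on this point.

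**2. Order of events.**

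| Step | Section | Before or after allocation |
|---|---|---|
| Phone call for allocation, when EVICEL is due | Randomisation/blinding | the dividing point |
| First spray, then implantation, cementing, functional tests | Details of the operation | after, if the call precedes the first spray |
| Second spray, 2 min wait, suturing | Details of the operation | after, on any reading |
| Time from incision to suturing is known | Details of the operation | after |
| Actual use of EVICEL departs from the agreement | Subject withdrawal | after |

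The randomisation section also places the call after conventional haemostasis, which the operative description mentions again later in the procedure. Even on that later reading, the wait and the suturing still follow allocation. The 2 h criterion therefore cannot be settled for every patient before the call, and Subject withdrawal concedes this by calling overrun foreseeable only in most patients. Non-enrolment for a deviation in EVICEL use cannot normally be applied before allocation.

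**3. How many patients.** The article gives no rate for overruns discovered after randomisation. Using its 1 % ceiling for non-inclusion as a stand-in:

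- expected number = 68 × 0.01 = 0.68
- P(at least one) = 1 − 0.99^68 = 0.495
- P(two or more) = 0.148

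**4. Effect of one removal on the estimate.** Assumption, not in the document: the removed EVICEL patient's Hb fall would have been d = 1 to 2 SD (15 to 30 g/l) above the mean of the other patients in that arm, and a comparable control stays in. Removal lowers the EVICEL mean by d/34:

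- 15/34 = 0.44 g/l
- 30/34 = 0.88 g/l

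The shift is towards EVICEL. In a simulation of 100,000 trials with no treatment effect (SD 15 g/l, unadjusted t-test), the rate of falsely concluding superiority rose from 0.025 with no removal to 0.032 (d = 15) or 0.038 (d = 30) with one such removal.

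**5. The alternative handling.** Statistical methods assigns a patient with no postoperative Hb the largest decrease seen in the control group, M. If a withdrawn EVICEL patient has no Hb and the true fall was x, the EVICEL mean moves by (M − x)/34. That counts against EVICEL whenever M exceeds x.

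**6. Power.** Removing one EVICEL patient (33 against 34) gives 0.897.

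**The case against.** The best defence is that the document's intention is clear enough. Two of the three passages keep long operations out before randomisation, the article expects the event to be rare, the primary population is correctly named as ITT, and the Hb samples are routine inpatient tests. If withdrawn means only that the patient is marked as off protocol while Hb is still collected or imputed, ITT can be met. Subject withdrawal already keeps patients transfused in theatre after randomisation, with an assigned value. All of this stands as far as it goes. It does not settle the residual cases, because nowhere is it said that a patient already randomised whose operation overruns stays in the analysis.

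Several stronger readings are tempting, and the document does not support them.

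- *Patients are withdrawn after randomisation as a stated rule.* The withdrawal sentence gives no timing; post-randomisation withdrawal is inferred from the sequence of events. For departures from the haemostatic procedure the text says excluded or not enrolled, never withdrawn.
- *Only EVICEL patients can deviate in EVICEL use.* A control patient given EVICEL would also deviate. Stopping the spray for a complication is described as ending the application, not as leaving the study.
- *All three sprays fall inside the 2 h clock.* The last follows suture of the joint capsule, and the article does not say whether the clock stops at the start or the end of suturing. Only the 2 min wait and the sprays before it clearly count.
- *The bias favours EVICEL.* That requires dropping the patient from the analysis. The worst-value imputation acts in the opposite direction.
- *Withdrawn patients will be replaced, or a missed late visit empties the PP set.* The study ends when "The study will be terminated when the necessary 34 patients per group have completed the study" applies, but no replacement rule exists and 68 is the recruitment number. The PP wording, "including all patients who completed the study according to the protocol", does not say which visits count, and that detail may properly sit in the full protocol or SAP.

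**Conclusion.** The point holds as an inconsistency that affects the primary analysis set. Three dispositions are given for one event, some instances can surface only after allocation, and removing or un-enrolling those patients is incompatible with analysing all randomised patients.

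Removals could differ by arm, because the surgeon knows the allocation and the 2 min wait and preceding sprays lengthen only EVICEL operations. This is a reasonable inference whose size cannot be derived, since the article contains no distribution of operating times. A reader might conclude that long operations are selectively taken out of the EVICEL arm; the text establishes only that nothing rules this out.

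The expected size is small: fewer than one patient at the 1 % ceiling, and a shift of under 1 g/l per patient against a planned 12 g/l. Both figures rest on stated assumptions: the ceiling applied to all 68 patients, and an Hb fall 1 to 2 SD larger in the removed patient. The direction depends on a handling choice that the article does not state. Loss of power is not a reason to act; the open choice after allocation is.

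**What to change.** Reconcile Study population, Details of the operation and of EVICEL administration, Subject withdrawal and Statistical methods by splitting the criteria at the randomisation call.

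- Criterion met before the call: the patient is not randomised.
- Anything arising after the call, including an overrun or a deviation in EVICEL use: the patient stays in the trial and in the ITT set, has all Hb samples to day 7 and all follow-up visits, is flagged as a deviation, and is left out of PP only.

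Remove the withdrawal sentence, and confine the non-enrolment wording to events before the call. No view is taken on the operating-time limit or on tourniquet management.

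The cost is wording only, and Trial status says that recruitment has not begun. The downside is that a few deviating patients remain in the primary analysis and slightly dilute the effect; the PP sensitivity analysis shows the result without them.

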#### Postoperative procedure

The postoperative procedure is described as follows:Prophylaxis against thrombosis is continued with certoparin-sodium 3,000 IU (or alternative) once daily until the patient reaches a physiological level of activity.The bandages are removed on day 1 after surgery. Physiological exercises, manual lymphatic drainage and mobilisation of the patient under full weight-bearing begin on day 1, according to the established in-house standard. Sutures are removed between days 10 and 14.The standard postoperative transfusion criterion at the site is an Hb level <6 g/dl, or in case of values between 6 and 8 g/dl, more than mild symptoms of anaemia. However, the criteria are soft and must be adapted according to the patient’s individual situation and his/her comorbidities, especially any cardiac comorbidities. The decision for or against a transfusion is therefore made by the treating anaesthetist or orthopaedic surgeon, according to their clinical experience. Thus, the unlikely possibility of transfusing patients with Hb levels between 8 and 10 g/dl cannot be completely ruled out. For each transfusion performed, the reasons will be documented precisely.Collection of blood parameters, their analysis and the documentation of the secondary endpoints are carried out as described in point 6 (Assessment of Efficacy). The amount of blood taken for each of the four blood tests is about 8.2 ml.

The following postoperative data are collected in the corresponding CRF (parameters marked with an asterisk are also assessed during the follow-up examinations):Blood parameters: Hb level 7 days postoperatively, CRP, leucocytesIn case of blood transfusions: number of units transfused, date of transfusion, Hb value before transfusion, reason for transfusionROM: angle of maximum flexion*Use of analgesics (WHO pain ladder)*Time when nerve block catheter is removed (if appropriate)Complications (for example, disorders of wound healing, thromboembolic events, signs of infection, for example, abnormal redness, swelling, pain, loss of function, hyperthermia)*Time when the wound is completely dry and any kind of secretion has ceasedDuration of hospital stayKSS and KOOS assessments* Type of rehabilitation after hospital stay (stationary, ambulant or other)* Number of physiotherapy treatment units after rehabilitation, including manual lymphatic drainage* Total costs of TKR Theoretical date of discharge (defined in section ‘Primary and Secondary Study Endpoints’)

